^ PM < 10 μm enter the respiratory tract, but may be the result of mechanical processes such as construction activities, road dust resuspension and wind whereas PM < 2.5 μm (fine particles) originate primarily from combustion sources such as smoking.
^
34
^ Quit rates and harm reduction are also outcomes which can be used to determine the impact of the intervention and will be reported as has been observed in other studies.
^
35
^
^,^
^
36
^

In order to assess the impact of the intervention on smokers perse FEV1/FEV6 was measured. This measure is a substitute for FEV1/FVC in diagnosing airflow obstruction and may better predict COPD-related pathology and morbidity.
^
37
^ The use of 6-s expiratory maneuvers makes handheld spirometry faster and easier, provides a more explicit end-of-test definition. Its use in primary care has also been demonstrated for the detection of COPD in adults.
^
38
^

Our intention is to enhance the application of evidence in the naturally occurring clusters which are the slums. Each of the slums is a unit with similar sociodemographic features where interventions can be more effective, compliance will be better and contamination less likely. We would like to capture the population level effects of the intervention. Thus, a cluster randomisation trial was chosen.

This study aims to assess the effectiveness of a “smoke-free home” intervention in partnership with women’s self-help groups in the slums of Kochi corporation, Kerala. This is a hybrid type 2 effectiveness-implementation research
^
39
^ combining the evaluation of effectiveness of the intervention and also assessing the implementation process. We hypothesize that a tobacco smoke-free home initiative in partnership with self-help group women will be effective in significantly reducing SHS in homes and SHS exposure among women and children of those homes over a period of 1 year. The specific aims are:
•To determine the effectiveness of an intervention led by women’s self-help groups to reduce indoor tobacco smoking by measuring urinary cotinine levels and reduction in indoor smoking by measuring PM 2.5 as an indicator for tobacco smoke in the home environment.•To correlate the urinary cotinine levels with the PM 2.5 in the indoor home environment.•To measure the effect of the intervention on the FeV1/FeV6 among smokers.•To explore the impact of the intervention on quitting rate, smoking intensity through in depth interviews and focus group discussions.

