In the next two months home visits will be conducted to paste the smoke free home stickers or distribute the calendars and reinforce the message of not smoking within homes and to get widespread recognition of the movement. Based on the findings of the baseline survey customized messages to quit will be delivered. The SHG-ASHA combined will also communicate the results of the cotinine levels and 2.5pm to the household members. The cotinine levels among the children and women will be an especially powerful tool to motivate and influence men to quit smoking within the homes and then to quit ultimately. If they express an interest to quit, they will be referred to the nearest urban primary health center for tobacco cessation. The influencers will be contacted again to encourage the smoker to quit smoking within home and to quit. Creating a movement and making “not smoking within the house an acceptable sociocultural norm” is the objective. At the end of the intervention as part of the dissemination activity smoke free homes declaration meeting for all community members in the presence of political leaders will be conducted.

*Control arm*: The other arm will get the standard of care which would include the routine programs which are being run by the government as part of the national tobacco control program such as training of health and social workers, NGOs, school teachers, and enforcement officers; Information, Education, and Communication (IEC) activities; school programmes; monitoring of tobacco control laws; coordination with Panchayath Raj Institutions for village level activities; and setting-up and strengthening of cessation facilities including provision of pharmacological treatment facilities at district level. Periodic assessments will be done at 10 and 16 months.

Health workers will conduct end-line surveys soon after the intervention and six months after the intervention in the intervention and control arm with the same questionnaire, urinary cotinine measurement and SHS measurement with an environmental sensor. Thus the measurements will be at 6, 10 months and 16 months respectively.

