*Baseline data*: The baseline data will be presented for both clusters and individuals as the risk of chance imbalances are greater with clusters.

*Numbers analyzed*: We plan to analyze 30 clusters with at least 300 indoor smokers in each arm. The urine cotinine of the women and children will be obtained from 300 women and or children in each arm. The indoor home values of 2.5 PM will be obtained from 300 households in each arm. Similarly, the lung function values as indicated by FeV1/FeV6 will be assessed among 300 each in the intervention and control group.

*Outcomes and estimation*: The difference in mean cotinine levels among the clusters in the intervention and control group with 95% CI will be estimated. The intracluster correlation coefficient for each outcome will be reported. Adjusted estimates of clustering will also be provided. Cox’s proportional hazards will be calculated for quitting, harm reduction, blood pressure values. This is to determine the effectiveness of an intervention based on partnering with women’s SHG’s to reduce indoor tobacco smoking by measuring urinary cotinine levels.

A repeated-measures ANOVA will be used to compare the mean urinary cotinine concentration between groups, before and after intervention.

Analysis for self-reported quit rates will be assessed by a Cox proportional hazards model. Generalised linear mixed effect models will be used to test between cluster differences from baseline to each follow up period for each outcome indicator.

We will use an intention to treat approach in analysis. A multilevel model will be used for analysis using the generalized linear mixed effect model which will also adjust for individual covariates. Key variables will be measured at baseline and then compared between arms to check balance; and if both arms are unbalanced with respect to any relevant factors, which can happen given that the unit of randomization is the cluster instead of the individual, those factors will be adjusted for in the final analysis so as to address potential confounding. Analysis for SHS exposure rates and quit rates will be assessed by a Cox proportional hazards model.

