•To correlate the urinary cotinine levels with the second-hand smoke in the home environment: correlation and linear regression analysis will be carried out by Pearson’s correlation if it follows a normal distribution and Spearman if it is a non-normal distribution.The difference in cotinine levels will be analysed by comparing the urine level of cotinine at the end of follow up, adjusted for the baseline value, by using linear mixed model or GEE to allow for cluster effect.•To measure the effectiveness of the intervention among smokers by measuring their FeV1/FeV6 using COPD6.To determine the effectiveness of the intervention in improvement of lung function the ratio of FeV1/FeV6 will be measured pre- and post-intervention and the mean difference between the groups will be assessed by a paired t-test.
**
*Qualitative data analysis*
**

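### The cotinine–PM2.5 association, a specific aim, is planned with methods that assume independent pairs; the resulting error is small in the simplest case and material if visits or household members are pooled

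*Protocol article*

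**What the plan says.** The specific aims at the end of the Introduction include: "To correlate the urinary cotinine levels with the PM 2.5 in the indoor home environment".

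The data analysis text under Outcomes gives this aim its own method: "correlation and linear regression analysis will be carried out", with Pearson's coefficient for normally distributed data and Spearman's otherwise. No term for slum, household or visit is attached. The next sentence of the same bullet turns to a different analysis, end-of-follow-up cotinine, and there specifies that it be "adjusted for the baseline value, by using linear mixed model or GEE to allow for cluster effect".

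Two more general sentences stand earlier under Outcomes: "Generalised linear mixed effect models will be used to test between cluster differences from baseline to each follow up period for each outcome indicator", and "A multilevel model will be used for analysis using the generalized linear mixed effect model which will also adjust for individual covariates". Neither mentions the association between cotinine and PM2.5.

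On the data structure:
- **Clusters.** Sample size calculation assumes an ICC of 0.06, about 20 indoor smokers per cluster, a coefficient of variation (CV) of cluster size of 0.45, and 15 clusters per arm.
- **Visits.** On timing, the Intervention section says: "Thus the measurements will be at 6, 10 months and 16 months respectively". This covers both urinary cotinine and the air sensor.
- **People per home.** The data collection text has urine taken from the woman and, where there is one, a child. The air monitor is placed in the home, so there is one PM2.5 record per home and visit.

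The protocol does not say which visit or visits, or which household member, enter the correlation. It mentions no interval or p-value for it.

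**The concern.** Pearson, Spearman and ordinary linear regression treat every pair as a separate piece of information. Here pairs can resemble each other because the homes are in the same slum, because the same home is measured again, or because two people in one home are set against the same PM2.5 value. If both variables are positively correlated within such groups, the usual standard error is too small. An association could then be reported with more certainty than the data carry.

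This is not a detail left to a later analysis plan: the protocol names the method. The same bullet allows for clustering in the neighbouring analysis, and the sample size was inflated for it. What is at stake is the credibility of the interval or test for one specific aim, not the comparison between arms.

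**Working it through.** **1. The plan's own figures.** The protocol gives no figure for the correlation aim, but its sample size shows how clustering was handled elsewhere. With mean cluster size m = 20, CV = 0.45 and ICC = 0.06:

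- VIF = 1 + ((CV² + 1)·m − 1)·ICC = 1 + (1.2025 × 20 − 1) × 0.06 = 1 + 23.05 × 0.06 = 2.383 (stated 2.4).
- 113 × 2.4 = 271 (stated 271); 271 / 20 = 13.6, so 14 clusters (stated 14).
- 271 / 0.9 = 301.1, that is 302; the protocol rounds to 300.

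These reproduce. The sample size allows for clustering; the correlation analysis does not.

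**2. Inflation for a correlation, one visit and one person per home.** With no true association, the variance of r is inflated by about

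1 + ((CV² + 1)·m − 1) × ICC(cotinine) × ICC(PM2.5) = 1 + 23.05 × product of the ICCs.

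The *product* matters, so the sample-size VIF of 2.4 does not carry over. Arm is constant within a slum (an ICC of 1), whereas PM2.5 varies from home to home.

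| ICC cotinine | ICC PM2.5 | Variance inflation | SE ratio | True rate of a nominal 5% test |
|---|---|---|---|---|
| 0.06 | 0.06 | 1 + 23.05 × 0.0036 = 1.083 | 1.04 | 6.0% (simulated 5.4%) |
| 0.06 | 0.2 | 1 + 23.05 × 0.012 = 1.277 | 1.13 | 8.3% |
| 0.06 | 0.3 | 1 + 23.05 × 0.018 = 1.415 | 1.19 | 9.9% |
| 0.2 | 0.2 | 1 + 23.05 × 0.04 = 1.922 | 1.39 | 15.7% (simulated 15.2%) |
| 0.3 | 0.3 | 1 + 23.05 × 0.09 = 3.075 | 1.75 | 26.4% (simulated 25.2%) |

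The protocol states only 0.06, and not for PM2.5. Every other ICC is an assumption.

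**3. More than one record per home.** The same rule applies: the inflation is 1 plus the sum, over the other records in the slum, of the product of the two correlations. Take cluster ICC 0.06 for both variables.

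- Three visits, total within-home correlation 0.3 for both: 1 + 2 × 0.09 + 23.05 × 3 × 0.0036 = 1.43, SE ratio 1.20.
- Three visits, within-home correlation 0.5: 1 + 2 × 0.25 + 0.249 = 1.75, SE ratio 1.32.
- Woman and child at one visit, sharing one PM2.5 value, cotinine correlation 0.5: 1 + 1 × 0.5 + 23.05 × 2 × 0.0036 = 1.67, SE ratio 1.29.
- Three visits with woman and child, within-home correlation 0.5: 1 + 0.5 + 4 × 0.25 + 23.05 × 6 × 0.0036 = 3.00, SE ratio 1.73.

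**4. Simulation.** There were 30 clusters of mean size 20 and CV 0.45, no true association, a Pearson test ignoring all structure, and 3,000 runs per setting (simulation error near 5% is √(0.05 × 0.95 / 3000) = 0.4 percentage points).

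| Records entered | Assumed correlations | Rejection rate | SE ratio |
|---|---|---|---|
| One visit, one person | cluster 0.06 | 5.4% | 1.02 |
| Three visits | cluster 0.06, home 0.3 | 8.6% | 1.17 |
| Three visits | cluster 0.06, home 0.5 | 13.1% | 1.32 |
| Woman and child, one visit | cluster 0.06, cotinine within home 0.5 | 12.9% | 1.30 |
| Three visits, woman and child | cluster 0.06, home 0.5 | 24.2% | 1.68 |
| Three visits, woman and child | cluster 0.2, home 0.5 | 46.3% | 2.74 |

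The simulated SE ratios agree closely with the hand calculation.

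**The case against.** **The protocol never says that visits are pooled.** This stands. A correlation at baseline, or one per visit, contains no repeated observations. A reader might infer from the three measurement times that all records go into one analysis, but the text gives only when measurements are taken. Likewise, the numbers-analysed text counts 300 women and/or children per arm beside 300 households, which does not establish that both members of a home enter against one PM2.5 value.

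**At the only stated ICC the effect is negligible.** This stands for one visit and one person per home, with 0.06 applied to both variables.

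**No test or interval is announced, and no arm comparison depends on this aim.** Both are true. Linear regression ordinarily yields an interval and a p-value, however, and a coefficient for a specific aim would normally be reported with some measure of precision.

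**The plan recognises clustering in general.** It does, but the general sentences concern outcome comparisons, and the sentence written for this aim names other methods. A multilevel analysis of the association cannot be read into it.

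**Mixing of slum-level and home-level signal.** A reader might also infer that ambient PM2.5 differences between slums would create a spurious association. Slum-level confounding is possible, but nothing in the protocol demonstrates it. Ambient variation unrelated to cotinine would tend to weaken the coefficient, not produce one.

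**Conclusion.** The concern holds in a conditional form. The protocol fixes, for a specific aim, methods that assume independent pairs, in data that are clustered by slum and may also be repeated within homes. The direction of the error is clear if the ICCs are positive: intervals too narrow and p-values too small.

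Its size is not fixed by the document. It runs from slight (variance inflation 1.08, rejection rate about 5.4–6%) through about 8–10% with a PM2.5 ICC of 0.2–0.3 and cotinine at 0.06, to about 9–24% or more if visits, household members or both are pooled. The PM2.5 ICC, the within-home correlations and the pooling are all assumptions. The unstated choice of records therefore largely decides whether the matter is trivial, and the named methods do not protect against the worse cases.

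The stronger statement, that the plan treats repeated observations as independent and that its inference is seriously wrong, goes beyond the text. The primary between-arm comparison is unaffected. This is a low-cost improvement to one aim, not a threat to the trial's main conclusion.

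**What to change.** 1. State which visit or visits, and which household member or members, enter the cotinine–PM2.5 analysis.
2. Analyse log cotinine on log PM2.5 (or the untransformed values, if suitable) with a linear mixed model or GEE that accounts for slum. Where a home contributes more than one record, account also for household and include a term for visit.
3. If a Pearson or Spearman coefficient is still reported, give it a confidence interval from a bootstrap that resamples whole slums.

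The cost is a change of wording and a little more analysis work, with no new data. The interval will be somewhat wider. The protocol reports that baseline collection is still under way, so the change can be specified in advance.

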### Sample size calculation

Based on previous studies we assume an ICC of 0.06.
^
43
^ To detect a minimal difference of 0.03ng/ml in cotinine levels between groups,
^
44
^ at 80% power with a two-sided alfa of 0.05, the estimated sample size was 113 indoor smokers per arm for individual randomization. Since one of the studies in the slum area of Ernakulam had found a prevalence of indoor smoking of 16% and considering slums above 100 households it is assumed that the expected number of smokers within household will be 20 per cluster with variability in clusters. Hence we estimated the sample size for unequal cluster size,
^
45
^ with a CV of 0.45 and VIF=2.4. The estimated sample size was 271 and 14 clusters per arm. Further we assumed a drop-out rate of 10%, the final sample size was rounded to 300 per arm and 15 clusters.

**
*Randomisation*
**

The trial has been registered in Clinical Trials Registry – India
CTRI/2021/06/034478.

A simple randomisation will be undertaken of the selected slums in the urban and peri-urban areas to receive intervention or not by a computer-generated random number list.

Allocation concealment: Allocation will be based on clusters and the allocation will be done after the baseline survey assessment by a statistician not directly related to the study. There is no allocation concealment. All the indoor smokers will be recruited and they will be selected before randomising clusters.

*Implementation*: Meetings will be conducted with the Kochi Corporation and District Medical Office regarding the objectives of the study. After the baseline survey, which will help to identify the indoor smokers, smoking practices, ventilation issues, and waste management practices, a simple randomisation will be undertaken of the selected slums in the urban and peri-urban areas to receive intervention or not.

The allocation sequence generation and the assignment of participants to the intervention will be carried out by the statistician and the investigators will enrol the participants.

*Blinding*: Blinding may not be possible as a lot of people are involved, local self-government officials, the investigators team, health centres, health workers, frontline workers such as the accredited social health activist, and anganwadi workers. The group of people who collect the outcome data will be blinded.

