### Outcomes

**
*Primary and secondary*
**

The primary outcome is SHS exposure at homes at 10 months and 16 months as assessed by the change in mean urine cotinine levels among women and or children of the smoker at the individual level. The secondary outcomes will include individual level self-reports of smoking within homes, particulate matter 2.5, harm reduction (reduction in the number of cigarettes smoked), quitting of smoking, blood pressure, Fagenstrom Nicotine dependence score, and comorbidities. Individual level assessment of Fev1/Fev6 will also be carried out with handheld spirometry considering a cut off of 73% to be indicative of COPD which is also a secondary outcome. Forced expiratory volume in 1 second (FEV1) is the maximum amount of air that the subject can forcibly expel during the first second following maximal inhalation.
^
46
^ Similarly, forced expiratory volume in 6 seconds (FEV6) is the volume of forcibly exhaled air measured during 6 seconds
^
47
^ which can be measured by handheld spirometry.

Cluster level assessment of 2.5 particulate matter in homes will also be done with air quality monitors. Monitoring and assessing intervention in terms of development of a training booklet, educational material, number of meetings organized, proportion of self-help group members in the area participating and inviting local self-government members to participate.

In order to understand the reasons for success and failure, in-depth interviews of men who have successfully quit smoking within homes, quit smoking completely, ASHAs, and health workers will be conducted. Focus group discussions of wives of smokers who quit smoking within homes and those who reduced the number of cigarettes will be conducted.

*Data analysis and statistical plan*: Data will be entered electronically on a secure file storage system and password protected. Data will be anonymised by assigning a unique identification number to each smoker. Outcome data will be reported in accordance with the Standard Protocol Items: Recommendation for Intervention Trials (SPIRIT). All the smokers will be included in the analysis regardless of reduction in smoking within homes.

**
*Participant flow*
**

30 clusters will be randomly assigned into two groups and will receive intended intervention and will be analyzed for primary outcome of urinary cotinine. For each group losses and exclusion of clusters and individual participants will be recorded (
Figure 1).

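### The between-arm difference in FEV1/FEV6 is assigned to a paired t-test, which cannot test it and ignores slum, in conflict with the protocol's own mixed-model statement

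*Protocol article*

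**What the plan says.** The Introduction lists as a specific aim "To measure the effect of the intervention on the FeV1/FeV6 among smokers". The Outcomes section makes the ratio a secondary outcome, "considering a cut off of 73% to be indicative of COPD which is also a secondary outcome". The list of objective-specific analyses at the end of that section takes the ratio before and after the intervention as the evidence of effectiveness on lung function. The method it names is this: "the mean difference between the groups will be assessed by a paired t-test".

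Three other statements bear on this:

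- **Who is compared.** Under Numbers analyzed, "the lung function values as indicated by FeV1/FeV6 will be assessed among 300 each in the intervention and control group".
- **How they were allocated.** Under Randomisation, "A simple randomisation will be undertaken of the selected slums in the urban and peri-urban areas". No matching or pairing of slums is described.
- **What else is promised.** The paragraphs on outcomes and estimation commit to generalised linear mixed models for every outcome indicator, comparing change since baseline at each follow-up. They also commit to reporting an intracluster correlation for every outcome. For cotinine, the item just before the lung-function one specifies a follow-up value adjusted for baseline, by linear mixed model or GEE, with clustering allowed for.

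Nothing ranks the lung-function sentence against the general mixed-model sentence.

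**The concern.** A paired t-test needs two measurements on the same unit. Smokers in the two arms are different people in different slums, so the test named for the between-group difference cannot be computed between groups. What can be run is before versus after within each arm. That discards the randomisation: anything that moves both arms alike, such as season or practice with the blowing technique, appears as change in the intervention arm. The test also treats smokers as independent although slums were randomised.

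At stake is the answer to one of the trial's stated aims. Two incompatible analyses are on the page, one of them invalid, and the choice between them would be open after the data are seen.

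**Working it through.** **1. Structure (no assumption needed).** The target is a difference between groups, the groups are 300 smokers each in separate slums, and allocation is simple randomisation of slums. No pair spans the arms, so the named test and the stated target do not fit together.

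**2. The protocol's own allowance for clustering.** Inputs from Sample size calculation: "Based on previous studies we assume an ICC of 0.06", mean cluster size m = 20, CV of cluster size 0.45, 113 per arm before inflation.

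- VIF = 1 + [(CV² + 1)m − 1] × ICC = 1 + [(0.2025 + 1) × 20 − 1] × 0.06 = 1 + 23.05 × 0.06 = 2.383 (stated: 2.4).
- 113 × 2.4 = 271.2 (stated: 271). 271/20 = 13.55, so 14 clusters, as stated.
- 10% dropout: 271/0.9 = 301.1, or 271 × 1.1 = 298.1 (stated, after rounding: 300).

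The plan's figures reproduce.

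**3. Error rate of a t-test that ignores slum.** True two-sided type I error ≈ 2 × [1 − Φ(1.96/√VIF)], with VIF = 1 + 23.05 × ICC. The 0.06 was set for the cotinine sample size. No ICC for FEV1/FEV6 change is given, so a range is shown.

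| ICC (assumed) | VIF | Type I error |
|---|---|---|
| 0 | 1.000 | 0.050 |
| 0.01 | 1.231 | 0.077 |
| 0.02 | 1.461 | 0.105 |
| 0.06 | 2.383 | 0.204 |

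Simulation (15 slums per arm, mean size 20, CV 0.45, 4,000 runs per setting) agrees. With no change, the within-arm paired test rejects in 0.078 at ICC 0.01 and 0.193 at ICC 0.06. A two-sample t-test on change that ignores slum rejects in 0.074 to 0.077 and 0.19 to 0.21.

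**4. Reading an effect from two within-arm tests.** Suppose there is no intervention effect, but both arms shift by the same amount, in units of the SD of change. Let p be the chance that one arm's paired test is significant (noncentral t, no clustering). The arms are independent, so the chance that the intervention arm is significant and the control arm is not is p(1 − p).

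| Shared shift (assumed) | p, n = 300 | p(1 − p) | p, n = 270 | p(1 − p) |
|---|---|---|---|---|
| 0.05 SD | 0.139 | 0.120 | 0.130 | 0.113 |
| 0.10 SD | 0.408 | 0.242 | 0.374 | 0.234 |
| 0.20 SD | 0.932 | 0.063 | 0.906 | 0.085 |

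The product cannot exceed 0.25, so the middle row is close to the worst case.

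**5. A valid comparison.** In the same simulation, a between-arm t-test on the slums' mean changes (15 versus 15) rejects in about 0.045 to 0.054 for ICC 0, 0.01 and 0.06, at shared shifts of 0, 0.10 and 0.20 SD.

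**The case against.** The strongest reply is that the general mixed-model sentence covers FEV1/FEV6, since it is a stated secondary outcome, and would give a cluster-adjusted randomised comparison. This stands in part. A reader might infer from the lung-function sentence that the trial's FEV1/FEV6 result is bound not to be a randomised comparison. The protocol does not support that, because the result depends on which statement is followed. The general sentence does not, however, remove a specific and contrary instruction for this endpoint.

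Second, the sentence names a between-group difference, so the test may simply be misnamed and a two-sample comparison of change intended. If so, step 4 falls away and shared trends cancel. The clustering error in step 3 remains.

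Third, the sizes rest on inputs that the protocol does not supply. Stable differences between slums cancel in a change score, so the ICC could well be below 0.06. The protocol nowhere says that an effect will be declared when one arm is significant and the other is not. A reader might therefore take the 24% or the 20% as the expected error of this trial. They are the upper parts of assumed ranges. Regression to the mean should also not be listed among the shared trends: smokers are enrolled on age, residence and indoor smoking, not on lung function.

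Fourth, this is a secondary outcome, and finer modelling detail may properly sit in an analysis plan that is not shown. Both points limit the severity. Neither excuses naming a test that does not fit.

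**Conclusion.** The point holds as an error in one sentence and a conflict between two. That the paired t-test cannot deliver the between-arm FEV1/FEV6 effect follows from the design alone. That it ignores clustering is equally plain, and the cost is an error rate of roughly 0.08 to 0.20 against 0.05 for assumed ICCs of 0.01 to 0.06. The misleading pattern in step 4, about 6% to 24% of trials at n = 300 for the shifts shown, arises only under within-arm testing and a decision rule that the protocol does not state.

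Both consequences apply only if the lung-function sentence is followed rather than the general mixed-model sentence. The cotinine analysis, the sample size and the data collection are not affected. Severity: moderate.

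**What to change.** Delete the paired t-test. Analyse follow-up FEV1/FEV6 adjusted for its baseline value by a linear mixed model or GEE with a slum effect, as the protocol already does for cotinine, with a small-sample correction for 30 clusters. Report the between-arm difference with its 95% CI. Align this item with the general mixed-model sentence, so that one analysis governs the endpoint. Before-and-after changes within each arm can still be tabulated as description, without being used to judge effectiveness.

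The cost is a change of wording. No new data, visits or participants are needed, and the Study status section says that baseline collection was still under way.
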